**Figure 1 figure1:**
[figure not shown]
First Version of Theory of Change Map.

#### Aim 3: Pilot Trial of the Intervention Packages

##### Overview

The aim of this phase of the project is to pilot the coproduced intervention packages developed in phase 2 of the project to assess their feasibility, acceptability, cost, and potential effectiveness. This phase will also assess the factors that facilitated and hindered the implementation of the piloted intervention packages and what needs to be learned before scaling up.

The pilot of the ARISE&WIN interventions has been planned as a quasi-experimental study with a prepost design. The design was chosen because there was unanimity around it being feasible while allowing us to draw conclusions about the potential effectiveness of various interventions. The study will consist of 3 arms. One of the intervention groups will receive the capacity building intervention package. The second intervention group will receive the social protection intervention package in addition to the capacity building intervention package. The capacity building and the social protection interventions will be finalized during the coproduction process. The third group will be a control group serving as a comparison group, and participants will not receive any intervention. The pilot will be conducted in the LGAs of Greater Ibadan, where situational analysis has been conducted. The LGAs will be stratified into urban, periurban, and rural LGAs and randomly assigned to 1 of the 2 intervention groups or the control group. On the basis of recommendations from literature [43,44] on pilot trials, a sample size of 120 participants would be large enough to assess feasibility and other outcomes of interest in the pilot study. To account for possible attrition, the sample size would be rounded up to 150 in total, with 50 participants per arm of the trial. Frequency matching will be conducted to ensure that across the intervention and control LGAs, the participants will have similar characteristics based on age and their sector of occupation. Participants will be recruited through advertisements on social media platforms where self-employed young women are active. Announcements will also be made at business association meetings to identify eligible participants. Participants will also be recruited through partner organizations (SMEDAN and the Centre for Support of Women in Unpaid and Informal Employment in Nigeria) that work with self-employed young women.

All groups will participate in a preintervention survey. Then, the interventions will be delivered over a period of 4 months. Follow-up surveys will be conducted at 6 weeks at the end of the capacity building intervention and months 4, 6, and 12. As part of a process evaluation, in-depth exit interviews will be conducted with approximately 20 participants to gain deeper insights into their perceptions about the interventions they receive. In addition, a survey will be administered to intervention facilitators while a subset of them will participate in in-depth interviews.

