**Methods:**

This multimethod project has 3 components. The first is a situational analysis of the impact of the pandemic and other significant life events on the work and well-being of self-employed young women vis-à-vis self-employed young men. This involves qualitative interviews with approximately 60 self-employed young women and men and a digital storytelling initiative to represent some of these stories in video format. Secondary data analysis of the Nigerian General Household Survey and the COVID-19 Longitudinal Phone Survey will be conducted. Furthermore, a scoping review of the impact of significant life events, including the COVID-19 pandemic, on self-employed workers in low- and middle-income countries will be conducted. The second component is the coproduction of interventions involving qualitative interviews with self-employed young women, members of their support network, and policy makers to find out their views on how to support self-employed women. It also entails an analysis of policies relevant to self-employed women in Nigeria and theory of change workshops to create a map for achieving the long-term goal of improving their resilience. Furthermore, a systematic review of interventions to improve the job quality and well-being of self-employed workers will be conducted. The third component is a pilot of the coproduced interventions in a quasi-experimental study involving 300 participants to assess feasibility, acceptability, cost, and potential effectiveness.

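### LGAs are allocated within urban, periurban and rural strata, but stratum enters neither the matching of women nor the stated comparison, so equal urban-rural mixes across arms are not guaranteed

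*Protocol article*

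**What the plan says.** The design is in the Protocol article, Aim 3: Pilot Trial of the Intervention Packages, Overview. Allocation is by area: "The LGAs will be stratified into urban, periurban, and rural LGAs and randomly assigned to 1 of the 2 intervention groups or the control group". The sample is set as a total per arm: "the sample size would be rounded up to 150 in total, with 50 participants per arm of the trial". Frequency matching across intervention and control LGAs is then meant to ensure that "the participants will have similar characteristics based on age and their sector of occupation". Stratum is not among the matching variables, and no count per stratum or per LGA appears.

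Recruitment is open: "Participants will be recruited through advertisements on social media platforms where self-employed young women are active", together with business association meetings and two partner organisations.

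The Analysis subsection of Aim 3 compares the three groups by chi-square tests and one-way ANOVA at P<.05, with Bonferroni-adjusted pairwise comparisons against control. Generalized linear models follow only if necessary, for confounders and for variables that differ at baseline. Education is the example given; urban-rural stratum is not mentioned.

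**The concern.** Stratifying the LGAs governs which kinds of area an arm contains. It does not govern how many of the arm's 50 women come from each kind. An arm with 35 urban women and an arm with 20 both satisfy every rule the article states.

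Open recruitment will fill places fastest where the channels are strongest, and that can vary from one LGA to the next. Place type plausibly affects earnings, savings, access to health care and social support, which are the secondary outcomes, and the sponsor thought it important enough to stratify by. At stake are some precision in each arm contrast and, where recruitment is uneven, a nominal error rate that the unadjusted test does not quite hold.

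**Working it through.** **Inputs from the article.** Three arms, 50 per arm, 150 in total, raised from 120; matching on age and sector; unadjusted comparison at 0.05.

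**The article's own figure.** 3 × 50 = 150. Going from 120 to 150 corresponds to 20% attrition (120/0.80 = 150), or to a 25% uplift (120 × 1.25 = 150). No attrition rate, effect size or power is stated, so nothing more can be reproduced. The Abstract gives a different size ("a quasi-experimental study involving 300 participants to assess feasibility, acceptability, cost, and potential effectiveness"). That conflict is a separate matter, so 100 per arm is shown below as well.

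**Assumed, because the article gives no figures.** Expected urban share p of 33% to 70%; urban-rural outcome gap of 0.2, 0.5 or 0.8 SD; differences in urban share matched by opposite differences in women from areas with rural-like outcomes.

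**Step 1: chance imbalance.** The SD of the difference in urban share between two arms is √(2p(1−p)/n).
- n = 50, p = 0.5: √(2 × 0.25/50) = 0.10, or 10 points.
- n = 100, p = 0.5: √(2 × 0.25/100) = 0.071, or 7 points.

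Simulating three arms with the same expected mix, for p from 33% to 70%:

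| Largest gap among three arms | 50 per arm | 100 per arm |
|---|---|---|
| at least 10 points | 59–64% of trials | 31–37% |
| at least 20 points | 9–14% | about 1–2% |

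**Step 2: uneven recruitment between LGAs.** Let each arm's underlying mix vary (Dirichlet, concentration c, expected urban share 50%). With c from 50 to 5, the SD of an arm's underlying urban share, √(0.25/(c+1)), runs from 7 to 20 points. In simulation the median largest gap among three arms is then 16 to 36 points, and a gap of 20 points or more occurs in 37–83% of trials. These concentrations are illustrative.

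**Step 3: shift in a contrast for a given gap.** Shift = difference in urban share × outcome gap. The 95% half-width at 50 per arm, ignoring clustering by LGA, is t(0.975, 98) × √(2/50) = 1.984 × 0.20 = 0.40 SD.

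| Difference in urban share | gap 0.2 SD | gap 0.5 SD | gap 0.8 SD |
|---|---|---|---|
| 10 points | 0.02 | 0.05 | 0.08 |
| 20 points | 0.04 | 0.10 | 0.16 |
| 30 points | 0.06 | 0.15 | 0.24 |

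At 20 points and 0.5 SD the shift is 0.10/0.40, a quarter of the half-width.

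**Step 4: what this does on average, not given a particular gap.** Take p = 0.5 and an outcome gap of 0.5 SD.
- Chance only: the shift has SD 0.5 × 0.10 = 0.05. The ordinary standard error, √(2/50) = 0.20, already contains it. Removing it would give √(0.20² − 0.05²) = 0.194, about 3% smaller.
- Uneven recruitment: the variance of the share difference is multiplied by (50+c)/(1+c). For c = 50 the factor is 100/51 = 1.96, the share SD 0.140 and the shift SD 0.070. For c = 5 the factor is 55/6 = 9.17, the share SD 0.303 and the shift SD 0.151. The part beyond chance is not in the ordinary standard error. The true standard error becomes √(0.04 + 0.070² − 0.05²) = 0.206 for c = 50 and √(0.04 + 0.151² − 0.05²) = 0.246 for c = 5. A nominal 0.05 test then rejects with probability 0.057 and 0.111 (normal approximation).

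**The case against.** Four points deserve weight.

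**Condensation.** The article compresses a large project, and stratum quotas may sit in a full protocol. Silence on women per LGA would be no finding. But the article does name the matching variables and does state the comparison, and the allocation factor is in neither. That is a choice on the page.

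**Random assignment.** A reader might infer that the arm comparison is systematically biased, or that stratifying the LGAs gives no protection. The article does not support either. LGAs are randomised within strata, so unless recruitment differs by arm, strong and weak channels fall on arms by chance and the expected difference in mix is zero. With enough LGAs per stratum, every arm also gets some of each type. The purely chance part is already covered by the usual standard error. This objection stands, and it is why the point is about precision and chance imbalance.

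**Adjustment is available.** All groups complete a preintervention survey, and the Analysis subsection allows adjustment for variables that differ at baseline. Stratum could qualify. But the provision is conditional and does not name stratum, so the default remains the unadjusted test.

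**Scale and timing.** The outcome gap is assumed. By chance alone a 30-point gap between a given pair of arms is a 3-SD event, about 0.3%, so a mostly urban arm facing a mostly rural one is not something to expect without markedly uneven recruitment. The outcomes most obviously tied to place are secondary, this is a pilot, and the Results section had recruitment finishing in January 2025. The article also sets no feasibility aim by stratum, so thin rural numbers would fail no stated objective. All this limits the seriousness, but not the case for analysing by the strata used in allocation.

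**Conclusion.** The point holds in a limited form. Stratified assignment of LGAs does not by itself guarantee that the arms have the same urban-rural mix of women, because stratum is carried into neither the participant matching nor the stated comparison.

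At 50 per arm the urban share of two arms differs by chance with an SD of about 10 points, and uneven recruitment adds to that. Under an assumed 0.5 SD urban-rural gap, a 20-point difference moves a contrast by 0.10 SD. On average the cost of pure chance imbalance is small, about 3% on the standard error. Under the illustrative uneven-recruitment scenarios, true type I error is about 0.06 to 0.11 against a nominal 0.05.

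The article supplies no stratum mix, number of LGAs or outcome gap, so the actual size cannot be settled from it. It is worth correcting because the remedy is cheap and amounts to analysing by the groups the trial already randomises within.

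**What to change.** **If any recruitment remains open:** add stratum as a marginal frequency-matching target, with the same stratum counts in every arm. The split is the sponsor's choice. Keep it marginal: crossing three strata with, say, two age bands and the five business types listed for the interviews would make 3 × 2 × 5 = 30 cells for 50 women, fewer than two per cell.

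**If recruitment has closed, as the Results section suggests:** report the urban, periurban and rural counts by arm. Then, before outcome data are compared, specify stratum as an unconditional term in the generalized linear models of the Analysis subsection, in place of the unadjusted comparison. Standardising each arm to one common stratum mix is an acceptable alternative.

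**Cost:** no extra participants, and only each woman's LGA as data. Matching may slow the filling of one stratum. The model term uses two degrees of freedom, leaving 145 of the 147 residual degrees of freedom in a three-arm comparison of 150 women.

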###### Sampling

Self-employed young women and men will be sampled from urban, periurban, and rural areas in the Ibadan metropolitan area using both purposive and snowball sampling techniques until theoretical saturation is reached. Self-employed young women and men will be sampled from various types of businesses, including services, commerce, craftsmanship, primary production, and manufacturing, and self-employed youth with various levels of educational attainment will also be included. They will be recruited through various trade and business-related associations and other economic or social networks. Self-employed youth who are particularly vulnerable, including those with mental and physical disabilities, and adolescents will be purposively sampled. The total number of planned participants for the semistructured interviews is 60, roughly evenly divided between women and men based on an estimate of the number of participants we think we need to reach theoretical saturation (informed by previous qualitative studies of similar topics) [20]. Interviews will be audio recorded and transcribed verbatim. Transcripts will be analyzed as the study is ongoing, and the team will meet and decide whether the sample size needs to be reduced if theoretical saturation is achieved earlier (ie, the same themes repeat across interviews) or increased if it is not achieved (ie, new themes are still emerging).

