##### Outcomes

The primary outcome of this study is well-being (financial, mental, and physical). Financial well-being will be measured using the Consumer Financial Bureau Financial Well-Being Scale [45]. Mental and physical well-being will be measured using the 9-item Patient Health Questionnaire [46], the 12-item General Health Questionnaire [47], as well as the 12-item Short-Form Health Survey [48].

The secondary outcomes that will be measured are earnings, savings, perceived social support, as well as access to health care. Earnings will be measured by asking questions about participants’ revenues, costs, and profits from their sales. Savings will be measured by asking about the various persons, institutions, or organizations with which they save; how frequently they save; and how much they save each time they do. Social support will be measured using the Multidimensional Scale of Perceived Social Support [49] and the Self-Employment Social Support Scale [20].

In order to understand the pathways through which the interventions could affect the outcomes, questions will also be asked, which evaluate the knowledge, attitude, and practices of the self-employed young women who participate in the intervention in the various domains of the intervention, including business management; the use of digital technologies; the management of their personal and business finances; the use of resources available to self-employed young women in Oyo State; and caring for their mental, physical, and social health. Questions will also be asked to find out the number of business associations and other social groups that self-employed young women belong to, whether they have been rescued from any dire situations (eg, domestic violence), and how many of them are enrolled in health insurance. Questions will also be asked to members of the support network of self-employed young women who participate in the intervention to assess changes in their knowledge, attitudes, and practices toward providing support to the self-employed young women in their lives. Furthermore, the pre- and postintervention survey will include 3 rated items and an open-ended question about the impact of the last experienced significant life event on participants’ ability to meet their needs and on their well-being and work.

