## Discussion

This is a gender-transformative project that will provide a greater understanding of the impact of the COVID-19 pandemic and other significant disruptive life events on the working lives and well-being of self-employed young women in Nigeria and the norms, attitudes, and structures that perpetuate gender inequity. Through a collaboration between the researchers, self-employed young women, policy makers, and other relevant stakeholders, the project will result in suitable and contextually appropriate gender-transformative interventions to enable young women to better cope with events that disrupt their work and well-being and improve their income security; their mental, physical, and social health; and their social support system. The interventions that will be developed will consider the perspectives and needs of women who are particularly marginalized, including those with mental and physical disabilities and those with little or no formal education. These interventions will differ from previous interventions for self-employed young women in this context because they will be coproduced, and intentional attention will be paid to gender dynamics in their design. The results of the pilot study will be used to ascertain the feasibility, acceptability, cost, and potential effectiveness of the coproduced intervention packages. The results of the pilot study will be used to refine the intervention packages in preparation for a large-scale efficacy trial.

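### The pilot's recruitment routes favour women who may already show some of the pathway behaviours, and the default analysis does not routinely use the preintervention value

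*Protocol article*

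**What the plan says.** The Overview under Aim 3 (pilot trial) gives three ways into the pilot:

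- social media: "Participants will be recruited through advertisements on social media platforms where self-employed young women are active";
- association meetings: "Announcements will also be made at business association meetings to identify eligible participants";
- partner bodies: "Participants will also be recruited through partner organizations (SMEDAN and the Centre for Support of Women in Unpaid and Informal Employment in Nigeria").

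The same section matches participants across LGAs by frequency on age and sector of occupation only.

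The Outcomes section sets well-being as the primary outcome. It then adds questions on the pathways through which the packages might work. These cover several domains ("including business management; the use of digital technologies; the management of their personal and business finances"). A further domain concerns local support: "the use of resources available to self-employed young women in Oyo State". Group membership is covered as well: "Questions will also be asked to find out the number of business associations and other social groups that self-employed young women belong to".

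The Analysis section compares study outcomes across the three groups by chi-square tests and one-way ANOVA, with Bonferroni-adjusted pairwise comparisons. Generalized linear models are fitted only if necessary, for confounders and for variables that differ at baseline. The Overview plans a preintervention survey for all groups.

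For the Aim 1 interviews, the Sampling section states: "Self-employed youth who are particularly vulnerable, including those with mental and physical disabilities, and adolescents will be purposively sampled". The pilot section has no counterpart. The Discussion says the interventions will take into account the needs of "women who are particularly marginalized, including those with mental and physical disabilities and those with little or no formal education".

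**The concern.** A woman who enters through a given route is more likely than others to show the behaviour that the matching pathway item measures. If many participants already have it, few are left who can gain it. A group comparison of follow-up values then loses sensitivity, and a flat result on the item is hard to interpret unless the preintervention value is used. The Analysis section does not make that use routine, because its adjustment is triggered by an observed imbalance.

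The second issue is reach. Feasibility, attendance and acceptability are main products of this pilot and are meant to inform scale-up. The recruitment measure is the percentage of the planned sample enrolled. That could reach 100% without showing whether the less connected women named in the Discussion were enrolled. Nothing stated records the channel, so a different channel mix between arms would go unseen.

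**Working it through.** **Routes against measures**

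| Route (Overview) | Trait favoured | Closest pathway measure (Outcomes) | Form of the measure |
|---|---|---|---|
| Social media | being online | use of digital technologies | knowledge, attitude and practice questions |
| Association meetings | association contact | number of associations and groups | count, no fixed maximum |
| Partner organizations | contact with support bodies | use of resources in Oyo State | knowledge, attitude and practice questions |

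No route selects directly on the management of finances, on health care practices, on insurance enrolment or on the primary outcome.

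**The plan's own size.** The Overview goes from 120 to 150 for attrition. The implied attrition is 1 − 120/150 = 0.20, and 120/(1 − 0.20) = 150 = 3 × 50, so the step reproduces. It leaves 120/3 = 40 women per arm. The Abstract gives 300 participants for the pilot. The two figures need reconciling; I use the Overview's.

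**How high could a baseline be?** Assume that a share s of the sample enters through the one route that guarantees an item, and that a fraction q of the others have it. The baseline is then s + (1 − s)q. For q from 0.2 to 0.6:

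- s = 1/3: 0.47 to 0.73
- s = 1/2: 0.60 to 0.80
- s = 0.8: 0.84 to 0.92

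A near-ceiling start therefore needs one route to dominate. The document gives neither s nor q.

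**What would a high baseline cost?** Assumptions: a yes/no item; n = 40 per arm; alpha 0.05/2 = 0.025 two-sided (two comparisons with control; the divisor is my assumption); controls stay at p; the package converts half of those without the behaviour, so the treated share is p + (1 − p)/2. With h = 2·asin√p_T − 2·asin√p_C, power = Φ(h·√(n/2) − 2.241).

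| Baseline p | Treated share | h | h·√20 | Power |
|---|---|---|---|---|
| 0.40 | 0.70 | 0.613 | 2.741 | 0.69 |
| 0.60 | 0.80 | 0.442 | 1.977 | 0.40 |
| 0.80 | 0.90 | 0.284 | 1.269 | 0.17 |

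**What does the preintervention value recover?** I simulated the same settings. Women who have the behaviour keep it, and no control woman acquires it. The follow-up-only test is chi-square on all 40 per arm. The uptake test is Fisher's exact test among women who lacked the behaviour at baseline, on average 40(1 − p) per arm.

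| Baseline | Women lacking it per arm | Follow-up only | Uptake |
|---|---|---|---|
| 40% | 24 | about 0.70 | about 0.99 |
| 60% | 16 | about 0.38 | about 0.89 |
| 80% | 8 | about 0.16 | about 0.31 |

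If 10% of control women who lack the behaviour also acquire it, the pairs become about 0.50 and 0.77, 0.25 and 0.52, and 0.11 and 0.16. The gain persists but shrinks, and at 80% it is small. None of these figures allows for clustering by LGA.

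**The case against.** A reader might infer that the pathway measures start near their ceiling. The document does not support that. It reports no baseline level. The routes are alternatives, so a woman recruited online need not belong to an association or know a support agency. Seeing an advertisement is not skill in using digital tools for business. Membership is a count without an upper limit, and several domains are not selected on at all.

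A reader might also infer that the pilot cannot speak for marginalized women. That too goes further than the text. The Discussion sentence describes what the interventions will consider, not whom the sample represents. One partner is a centre for women in unpaid and informal employment, and rural and periurban LGAs are included. The contrast with Aim 1 is also weaker than it looks, because those interviews recruited partly through trade associations.

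The stakes for inference are limited. Pathway items are neither primary nor secondary outcomes, the pilot was not sized for them, and the power figures describe an invented yes/no item. The same routes serve all arms, so bias between arms is a possibility and not a finding. The design is described as prepost, and the generalized linear models leave room for baseline adjustment.

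All of this stands, and it confines the point to three things: the default analysis does not commit to the baseline value, the channel is not stated to be recorded, and the reach of the conclusions is not stated.

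**Conclusion.** The point holds in a limited form. The three routes favour connected women, and the traits they favour lie close to some of the exploratory pathway measures. A ceiling on those items is possible but not shown, and the primary outcome would not be affected directly. What can be improved is the default comparison. Under the assumptions above, using the preintervention value raises power on a yes/no item from about 0.38 to 0.89 at a 60% baseline, and from about 0.16 to 0.31 at 80%, with smaller gains if controls also acquire the behaviour.

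This rests on two readings: that the pathway items are analysed by the same default methods as the other study outcomes, and that they are asked of all three arms in the preintervention survey. The Outcomes section describes the knowledge, attitude and practice questions as put to women taking part in the intervention, so the second reading should be confirmed.

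For feasibility, attendance and acceptability the consequence is one of generalizability: the results describe women whom these routes can reach.

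**What to change.** The Results section says recruitment was due to end in January 2025 and the packages are being delivered, so the changes below leave recruitment and matching as they are.

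1. **Analysis of the pathway items.** State that digital use, association membership and resource use will be analysed with the preintervention survey. For yes/no items, compare uptake among women who lacked the behaviour at that survey. For counts and scores, adjust for the baseline value. Report the baseline distribution by arm, so that any ceiling is visible. Cost: protocol or analysis-plan wording, and a smaller denominator for the uptake items (about 8 women per arm if 80% already have the behaviour).
2. **Recruitment channel.** Record how each woman was recruited, retrospectively if needed, for example by one question at a follow-up survey. Report it by arm, and include it among the adjustment variables if it differs between arms. Cost: one question, with some recall error.
3. **Reach of the conclusions.** State that the feasibility, attendance and acceptability conclusions apply to women reachable through these routes, and report the schooling and disability status of those enrolled. Cost: wording and table rows. Education is already a planned background characteristic; disability needs one added question if it is not yet collected.
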